#### Outcomes

The primary outcome of the study will be the absolute number of episodes of
RRT triggering in a timely manner, defined by any triggering that occurred
in the units randomized to the study and for which the patient had critheria
within a 24-hour window. Appropriate time will be considered if the RRT
appears at the bedside within 5 minutes after the yellow code is triggered
by a health professional. The triggering time as well as the arrival time
are recorded by the care team on a specific form attached to the patient’s
medical record.

The identification of whether the yellow codes were activated properly will
be verified by a care team not participating in the study. This verification
will be carried out by checking the codes identified by a specific platform
provided by the company *Eritel Telecomunicações
Ltda.* (Eritel Telecommunications Limited)
*versus* the codes recorded in the medical record. If the
platform originates a code, but it was not confirmed/effective according to
the nursing team’s verification, it will be considered false triggering
(improper triggering).

The following secondary outcomes will be considered: mortality rates, cardiac
arrest, need for ICU hospitalization (defined according to institutional
protocols and trained staff) and duration of hospitalization during the
study.

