#### Data collection methods

In addition to the data regarding the recruitment period, information will be
collected to describe the characteristics of the clusters and patients
hospitalized in the selected wards for a period of three months prior to the
beginning of the protocol: January 2021, February 2021 and March 2021. The
institution’s Department of Epidemiology will provide the following
variables from institutional records (if available).

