#### Cluster-level data

Baseline variables (at the time of hospitalization): age, sex, type
of hospitalization (surgical or clinical).Outcomes (during hospitalization): number of RRTs triggered, yellow
code rates, in-hospital mortality, duration of hospitalization, need
for ICU hospitalization, and number of cardiac arrests.

We will also present the total number of RRTs triggered in this period (at
the hospital level) and the number of hospital admissions on the selected
wards both in this period and during the study.

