#### Statistical analysis

The demographic and clinical characteristics of the sample will be summarized
according to the groups in absolute and relative frequencies for the
categorical variables; continuous variables will be presented by position
statistics (mean, median) and scale (standard deviation and interquartile
ranges).

The analysis for the primary outcome (events that trigger the RRT in a timely
manner) will be conducted with a logistic regression model considering
binomial distribution from generalized estimation equations, considering a
uniform work correlation matrix between patients of the same ward adjusted
for the baseline number of episodes of RRT triggering in an appropriate
timely manner. Other outcomes will be compared using a similar methodology
considering the response distribution that best fits the data. All results
will be presented considering measures of effect with respective 95%
confidence intervals.

Sensitivity analyses for the primary outcome considering time series
assessments and time of RRT activation (weekday *versus*
weekend; night *versus* day shifts) will be performed
comparing treatment groups. The results will be presented in graphs with
monthly indicators.

It is not expected that there will be a large amount of missing data.
However, if some of the primary and secondary outcomes are missing, the
missing data rate will be reported by group, and the values will be imputed
by chained equation multiple imputation methods using the mice package with
sample base characteristics.

All analyses will be performed with statistical R software 4.0.2 (R Core
Team, Vienna, Austria, 2020). Interim analyses or the participation of a
Data and Safety Monitoring Committee (DSMC) are not foreseen in the
protocol.

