trial, the effectiveness of an automated vital signs monitoring system
associated with the automatic activation of the RRT on the absolute number
of triggers in an appropriate timely manner. Additionally, we will assess
clinical outcomes (mortality, cardiac arrest, need for ICU hospitalization
and duration of hospitalization) in an exploratory manner according to the
study groups. The assessment of RR manually is a limitation of this study,
considering that it is usually the least documented vital sign strongly
related to measurement errors;^(25)^ in this sense, the number of RRT activations might
be impaired. The unicentric characteristics and the small sample size are
other limitations of this protocol. Considering that we had no knowledge of
the intraclass correlation coefficient to make the appropriate formal
calculation for the cluster design, the sample size calculation was only a
preliminary estimate, characterizing this study as exploratory; on the other
hand, statistical analyses should adjust for the baseline values of RRTs in
the participating wards, which should reduce the random error of the
estimates. Additionally, the selection of the primary outcome was made
taking into account the exploratory design of this trial. We hope that from
the results obtained, it will be possible to carry out a multicenter study
with greater coverage so that we can confirm our findings. Another potential
limitation is performance bias, since it is an open-label study because of
the nature of the intervention. However, all other procedures involving the
management of patients in the wards will be maintained at the discretion of
the medical and nursing teams involved in the assistance. In addition, we
chose objective outcomes, and the team performing data collection and
statistical analysis will be blinded to the participant’s group, minimizing
the effects of this potential bias on the results.

The recruitment of the study was completed in September 2021. Currently, the
Hillrom study is in the data collection phase, identifying RRTs that have
been properly triggered. The study is expected to end in August 2022.

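### The primary logistic GEE adjusts for each ward's raw baseline count of timely activations, which mixes volume with timeliness, is not a listed baseline variable, and does not support the claimed gain in precision

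*Protocol article*

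**What the plan says.** All references are to the protocol article.

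- **Statistical analysis.** The primary model is a logistic regression with "binomial distribution from generalized estimation equations, considering a" uniform working correlation within ward. It is adjusted "for the baseline number of episodes of RRT triggering in an appropriate" timely manner. This is the only covariate named.
- **Outcomes.** The endpoint itself is worded as a count: "The primary outcome of the study will be the absolute number of episodes of" timely triggering. The model and the sample size calculation both work with a proportion.
- **Data collection methods.** Baseline covers three months before the "beginning of the protocol: January 2021, February 2021 and March 2021. The" institution's epidemiology department supplies the "variables from institutional records (if available").
- **Cluster-level data.** The listed baseline outcomes are "number of RRTs triggered, yellow" code rates, in-hospital mortality, length of stay, ICU need and cardiac arrests. Neither a number nor a proportion of timely activations is listed.
- **Discussion and trial status.** The authors say that the intraclass correlation was unknown and call the sample size preliminary. They then set against this an adjustment for the baseline RRT values of "the participating wards, which should reduce the random error of the" estimates. Timeliness is not part of that description.

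**The concern.** A covariate helps a model for a probability if it predicts that probability. A raw number of timely episodes is the product of how busy a ward is and how often its activations are timely, so a busy ward scores high whatever its timeliness. The covariate as named cannot be built from the variables listed for baseline, and two sections describe it differently, so two analysts could fit different primary models.

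The Discussion also gives the adjustment a job: it is the one feature set against the missing intraclass correlation. If the covariate is mostly noise and there are only six clusters, it may add error to the estimate. The standard GEE variance is already unreliable with six clusters and may not show that added error. The primary confidence interval and any claim of superiority are at stake.

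**Working it through.** **1. The plan's own figure.** Inputs from Sample size calculation: 70% against 88% timely, 90% power, 5% significance (taken as two-sided), and 1:1 allocation from Trial design.

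n per arm = [1.96·√(2·0.79·0.21) + 1.2816·√(0.70·0.30 + 0.88·0.12)]² / 0.18² = (1.129 + 0.720)² / 0.0324 ≈ 105.5, so 106 per arm and 212 in all. Power at 108 per arm is 90.7%. The stated 216 reproduces. The calculation treats activations as independent and contains neither a design effect nor a covariate.

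**2. How much information baseline holds.** 12 activations a month over six wards × 3 months = 36, or 6 per ward. At 70% timely, about 4.2 per ward are timely. The standard error of one ward's baseline proportion is √(0.70·0.30/6) ≈ 0.19, about as large as the 0.18 effect sought.

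**3. What the count encodes.** A ward with 6 of 6 timely (100%) and a ward with 6 of 12 timely (50%) both enter the model with the value 6.

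**4. The planned GEE, simulated.** The document gives neither the between-ward variation nor the ward volumes, so these are assumed ranges. Setting: six wards, three per arm, 2 activations per ward per month, three baseline months, about 216 trial activations, exchangeable logistic GEE, sandwich standard error, z interval.

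| Simulation | Effect of adding the baseline count |
|---|---|
| 70% vs 88%; logit SD 0 to 1.0; ward-volume CV up to 0.4; volume–timeliness correlation −0.7 to 0.7; about 400 runs per scenario | True SD of the estimate +8% to +25%; median interval width +3% to −28% (narrower in 8 of 9 scenarios); coverage of the 95% interval from 74–85% down to 66–74% |
| No true difference; logit SD 0.3 to 1.0; 250 runs per scenario | True SD about +10% to +50%; reported standard error lower; type I error from 14–24% up to 24–34% |

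With 250 runs, the Monte Carlo standard error of a 20% rejection rate is √(0.2·0.8/250) ≈ 2.5 points, so the ranges are approximate. The direction is not in doubt.

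**5. A ward-level t interval, for contrast.** With six wards and two arms, one covariate cuts residual degrees of freedom from 4 to 3. The critical value goes from 2.776 to 3.182, a 15% wider interval from that alone. In 20,000 runs per scenario the change in median width was:

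| Logit SD between wards | Baseline count | Baseline proportion |
|---|---|---|
| 0 to 0.3 | about +26% | about +25% |
| 0.6 | +14% to +23% | +14% |
| 1.0 | +5% to +18% | −5% to −1% |
| 1.5 | 0% to +1% | about −23% |

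A proportion costs as much as the count when wards are similar. It helps only when they differ strongly.

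**The case against.** Several points on the other side have weight.

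- **A reader might infer that the adjustment simply widens the interval.** That is true of a ward-level t interval, which the protocol does not plan. Under the planned GEE with a sandwich z interval, the reported interval mostly gets narrower. The fault there is an interval that is too narrow for a larger true error.
- **A reader might infer that adjustment always does the opposite of what is claimed.** The document does not support this. The between-ward variation is unknown. In the ward-level analysis at a logit SD of 1.5 the count is neutral, and a baseline proportion would help. What can be said is that the claimed gain is unsupported.
- **A reader might infer that the covariate cannot be obtained.** The article condenses a fuller protocol, and Outcomes says that trigger and arrival times are written on a form in the medical record. Baseline timeliness may be recoverable. The supportable statement is that it is not among the listed baseline variables.
- **The Discussion wording may be shorthand** for the covariate in the Statistical analysis section, and the Discussion does not say that adjustment replaces a design effect. Both are fair. The two descriptions still need to be made the same.
- **The count is not the main driver.** Much of the cost comes from adding any weak covariate with six wards, and type I error is already 14–24% without it. This stands, and it is why switching to a proportion is not a sufficient repair.
- **The study is labelled exploratory.** That softens the consequences, but it justifies neither a mis-specified covariate in the primary model nor the precision claim.

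**Conclusion.** The point holds in this form. The primary model uses a raw count where the modelled quantity is a proportion, the count is not a listed baseline variable, and the Discussion names the covariate differently. The statement that adjustment should reduce random error is unsupported with six wards and about 6 baseline activations in each.

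Over assumed ward logit SDs of 0.3 to 1.0, and with an uncorrected sandwich z test, the count moves type I error from roughly 14–24% to 24–34% while the reported interval mostly shrinks. With a ward-level t interval, width rises by 0–26% instead. Both results rest on assumed between-ward variation and ward volumes, and the GEE figures also assume no small-sample correction, since the article mentions none. A correction in an unseen analysis plan would change the GEE figures. It would not change the mismatch between a count and a proportion, or the gap in the baseline list.

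**What to change.** 1. Take the raw baseline count out of the primary model. Make the primary comparison unadjusted for this covariate, with inference suited to six clusters (a small-sample-corrected GEE or a ward-level t comparison).
2. Use baseline only in a sensitivity analysis, entered as each ward's timely proportion (timely / total), and use the same definition in the Statistical analysis and Discussion sections.
3. Add timely and total activations per ward to the Cluster-level data list. If baseline adjustment is kept as primary, lengthen the look-back. Twelve months, for example, would give 12 × 12 / 6 = 24 activations per ward and a standard error of √(0.21/24) ≈ 0.09 in place of 0.19.
4. Delete or qualify the Discussion's statement on random error.

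**Cost.** A change of model wording and two fields in a retrospective extract, with some form review if arrival times must be read from records. No further recruitment is needed, and the article places analysis after data collection.

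**Downside.** A chance baseline imbalance between wards is then handled only in the sensitivity analysis. If wards differ strongly (logit SD about 1 or more), a primary adjustment for the baseline proportion could have gained some precision.

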#### Ethical issues

This study was approved by the Research Ethics Committee (REC) of HCor under
CAAE no. 26298019.4.0000.0060. Amendments and specific changes to the
protocol will be carried out according to its progress and duly forwarded to
the institutional REC (previous versions: 1st version - November 2019; 2nd
version - September 2020; 3rd version - November 2020). Audits are not
planned for this protocol; however, the sponsor may require information and
reports during the conduct of the clinical trial and after its
completion.

Considering that the collection and evaluation of the study variables as well
as the triggering of RRTs are routines in clinical care practice and that
the data will be collected through medical records, the REC-HCor was asked
to waive the Free and Informed Consent Form for this research protocol.
However, the investigators obtained institutional authorization to carry out
the same.

There is minimal risk of loss of confidentiality associated with the study.
The risk will be minimized by using traditional precautions for the storage
of paper records and electronic records. Patient identifiers will not be
used in reports or publications of this study.

#### Dissemination policy

After the publication of the results, we will disseminate the study to the
entire care team of the participating center and to the sponsor through
face-to-face and/or virtual presentations. We will also present the results
at important congresses and events in the area.

#### DISCUSSION AND TRIAL STATUS

The measurement of vital signs is a fundamental component of patient
assessment, providing the basis for clinical decision-making from treatment
to hospital discharge. Therefore, these data must be accurate and quickly
accessible so that safe decisions can be made.^(16)^ In an American university hospital, error
rates were evaluated for electronic documentation of vital signs compared to
manual records on paper. As a result, it was found that the use of the
system reduced vital signs recording errors by more than half compared to
traditional manual documentation (error rates: 4.4% and 10%,
respectively).^(17)^
In addition, the implementation of the automated clinical documentation
system allowed the nursing team to increase the time spent on direct patient
care.^(18)^

Despite the lack of consistent evidence showing the effectiveness of RRT
systems on clinical outcomes, they have been implemented at hospitals
worldwide.^(6)^ After
the introduction of RRTs in a large Brazilian nonprofit hospital, a
significant reduction in waiting time for ICU beds among inpatients who
could not be admitted immediately after indication was determined, as well
as an increase in the recognition of palliative care patients; however, no
difference in hospital mortality was detected.^(19)^ Similar results were observed after the
implementation of RRTs in a Brazilian university hospital, where a reduction
was observed in in-hospital cardiac arrest but not in hospital
mortality.^(20)^

Electronic systems for automated notification of vital signs may contribute
to reducing call delays, one of the most important barriers to successful
implementation of RRTs^(21)^
associated with increased hospital mortality.^(22)^ In addition, they may increase the number
of RRT activations. In a before-and-after study conducted in wards in the
UK, the use of an electronic vital signs monitoring solution increased RRT
activations from 405 to 524 (p = 0.001). In addition, a decrease in overall
mortality and in the number of cardiac arrests was observed during the
protocol intervention period.^(23)^ However, it is noteworthy that before-and-after
studies are susceptible to a number of methodological biases compared to
randomized trials, which can ultimately invalidate the results or impair the
clinical significance of the study.^(24)^

The Hillrom study aims to evaluate, through a cluster randomized clinical
trial, the effectiveness of an automated vital signs monitoring system
associated with the automatic activation of the RRT on the absolute number
of triggers in an appropriate timely manner. Additionally, we will assess
clinical outcomes (mortality, cardiac arrest, need for ICU hospitalization
and duration of hospitalization) in an exploratory manner according to the
study groups. The assessment of RR manually is a limitation of this study,
considering that it is usually the least documented vital sign strongly
related to measurement errors;^(25)^ in this sense, the number of RRT activations might
be impaired. The unicentric characteristics and the small sample size are
other limitations of this protocol. Considering that we had no knowledge of
the intraclass correlation coefficient to make the appropriate formal
calculation for the cluster design, the sample size calculation was only a
preliminary estimate, characterizing this study as exploratory; on the other
hand, statistical analyses should adjust for the baseline values of RRTs in
the participating wards, which should reduce the random error of the
estimates. Additionally, the selection of the primary outcome was made
taking into account the exploratory design of this trial. We hope that from
the results obtained, it will be possible to carry out a multicenter study
with greater coverage so that we can confirm our findings. Another potential
limitation is performance bias, since it is an open-label study because of
the nature of the intervention. However, all other procedures involving the
management of patients in the wards will be maintained at the discretion of
the medical and nursing teams involved in the assistance. In addition, we
chose objective outcomes, and the team performing data collection and
statistical analysis will be blinded to the participant’s group, minimizing
the effects of this potential bias on the results.

The recruitment of the study was completed in September 2021. Currently, the
Hillrom study is in the data collection phase, identifying RRTs that have
been properly triggered. The study is expected to end in August 2022.
